MDA is an abused drug with poorly documented effects. The risks of modest single oral doses of MDA to healthy experienced volunteers is low, while the potential benefits to society of improved understanding of MDA pharmacology are high.

4.	METHODS: 

This is a double-blind, placebo-controlled clinical study occurring in a hospital setting.  The study uses a Latin-square balanced design.  Physiological, pharmacokinetic, hormonal, genetic, subject-rated, observer-rated, and behavioral measures are made at timed intervals before and after study drug administration.

(4a) General Study Design:  

The study uses a double-blind, placebo-controlled, Latin-square design.  Volunteers will be 12 healthy people not DSM-IV dependent on any substance (other than nicotine or caffeine).  All must have self-report experience with either MDA alone or have used separately both MDMA and a hallucinogen, such as LSD or psilocybin.  After careful screening at our laboratory, subjects will be admitted to the Clinical and Translational Science Institute Clinical Research Center (CCRC) at San Francisco General Hospital (SFGH). for 4 days and 3 nights.  Subjects are admitted to the CCRC the day before the first experimental session.  Experimental session 2 occurs 24 hours after the first dosing session, and final measures are collected on the 4th day. Subjects will be discharged on the 4th day in the late afternoon or early evening.  On the experimental dosing days subjects are dosed at approximately 10am and measures/data are collected at set time points throughout the inpatient stay.  Screening and the End of Study Visit take place in our laboratory and the inpatient portion of the study occurs at the CCRC at San Francisco General Hospital (SFGH).  Dosing takes place at approximately 10 am each day.  Sessions begin 24 hours apart on consecutive days and each session follows the exact same time course.  Subjects will come for follow up at APRL on one occasion between 1-4 weeks after discharge for additional safety monitoring. Briefly, the time schedule for the study is shown in Table 1, below.

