Repeated measures ANOVA will be used, employing similar strategies as in our other experiments.  Measures for hypotheses are continuous and are analyzed by ANOVA with time as the repeated measure and dose as a between subject factor. After a significant F test, post hoc pairwise comparisons will be performed using Fishers Least Significant Difference (LSD) test.  Effects will be considered statistically significant at P≤0.05.  Data from this and our other MDA studies will be pooled and a population PK/PD models will be fitted to the data using the program WinNonLin (36-39).  A compartmental model will be fitted to MDA, HMA and other metabolite concentration versus time data.  Population pharmacodynamic models will be fitted to the response versus time data, conditioning on the individualized Bayes estimates of the MDA/HMA parameters.

Sample Size: The aims of this experiment are to investigate the pharmacokinetics and pharmacodynamics of MDA. For pharmacokinetics, the data analysis primarily requires a descriptive approach rather than null hypothesis testing. We therefore powered the study based on pharmacodynamic measures, specifically self-report measures (because these tend to show more variation and smaller effects sizes than cardiovascular or neuroendocrine measures after MDA and other compounds similar to MDMA). Feelings of insight are a typical effect of hallucinogens and MDMA-like drugs. After 1.5 mg/kg MDMA, visual analog ratings for this item increased by 28±19 points compared to placebo. This was one of the smaller changes in visual analog items detected after MDMA. To detect a similar change after MDA, a sample size of 11 is required, with a power of 0.80 and assuming a two-sided alpha of 0.05. We will increase this N to 12 to allow balancing of dose order. This sample size should leave us adequately powered to detect changes in other measures. Measures are analyzed using repeated measures ANOVA with condition and time as factors. Sample size is too small to allow analysis of gender effects, so we will not balance gender but will conduct exploratory analyses if there appears to be a gender effect.

	(4d) Subject Selection:  

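### The stated requirement of 11 subjects for 80% power does not follow from a change of 28±19 points; N = 12 is enough on either SD reading, but its stated basis is wrong.

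*Protocol*

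**What the plan says.** The Sample Size paragraph of protocol section 4c says that pharmacokinetics will be handled descriptively, so the study is sized on self-report measures. The anchor is a visual analog rating of insight after 1.5 mg/kg MDMA: "visual analog ratings for this item increased by 28±19 points compared to placebo". From this the paragraph derives its requirement: "To detect a similar change after MDA, a sample size of 11 is required, with a power of 0.80 and assuming a two-sided alpha" (set at 0.05). It then adds one subject: "We will increase this N to 12 to allow balancing of dose order". It closes with a general assurance: "This sample size should leave us adequately powered to detect changes in other measures".

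The paragraph does not say whether ±19 is an SD or a standard error, or whether it belongs to the within-subject difference or to each condition. It names no test for the power calculation and gives no within-subject correlation.

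The design is in section 4a: "The study uses a double-blind, placebo-controlled, Latin-square design". Section 4b gives each subject two sessions on consecutive days, one condition per session, placebo or MDA. Every subject therefore contributes to both conditions.

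**The concern.** The ± is attached to a change relative to placebo, so the natural reading is mean ± SD of that change. This is a standardised effect of nearly 1.5, for which a paired comparison needs far fewer than 11 subjects. A required number close to twice what its inputs imply suggests that an input, the test or the power was something other than what is written.

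This is the only power figure in the protocol, and the assurance about all other measures rests on it. If the figure cannot be traced, a reader cannot tell what size of effect 12 subjects can detect on any measure.

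**Working it through.** **Inputs, all from section 4c (Sample Size):** difference 28 points; spread 19; two-sided alpha 0.05; power 0.80; stated requirement 11; planned N 12. The crossover design is from sections 4a and 4b.

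**Formula.** For a paired t-test on n subjects, with d = difference / SD of the difference, power is the probability that a non-central t variable with n − 1 degrees of freedom and non-centrality d√n exceeds the two-sided 5% critical value in absolute size. A two-period crossover analysis that also fits period uses n − 2 degrees of freedom.

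**Step 1. Try to reproduce 11, with 19 as the SD of the difference.** d = 28/19 = 1.474.

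| n | d√n | Power |
|---|---|---|
| 5 | 3.30 | 0.696 |
| 6 | 3.61 | 0.820 |
| 11 | 4.89 | 0.992 |
| 12 | 5.10 | 0.996 |

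The requirement is 6, or 7 with n − 2 degrees of freedom. The stated 11 is not reproduced.

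**Step 2. Take 19 as the SD within each condition.** The SD of the difference is then 19√(2(1 − ρ)), where ρ is the within-subject correlation. The protocol gives no ρ, so a range is shown.

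| ρ (assumed) | SD of difference | n for 80% power |
|---|---|---|
| 0.5 | 19.0 | 6 |
| 0.3 | 22.5 | 8 |
| 0.1 | 25.5 | 9 |
| 0 | 26.9 | 10 |
| −0.1 | 28.2 | 11 |
| −0.2 | 29.4 | 11 |

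At ρ = 0, d = 28/26.9 = 1.04. Power is 0.782 at n = 9, 0.834 at n = 10, 0.875 at n = 11 and 0.907 at n = 12. The requirement is also 10 with n − 2 degrees of freedom (power 0.822).

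**Step 3. What would make 11 right?** A paired test with n = 11 has 80% power at d = 0.938, so the SD of the difference would be 28/0.938 = 29.9. With n = 10 the matching figures are d = 0.996 and SD 28.1. So 11 is the smallest sufficient number only if that SD lies between about 28.1 and 29.9. If 19 is a per-condition SD, this means a negative correlation between two ratings from the same person, about −0.09 to −0.23. Otherwise another input must change: power 0.85 under the ρ = 0 reading gives 11, and so does power 0.90 with two-sample arithmetic counted per condition. The protocol states 0.80.

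**Step 4. If ±19 were a standard error.** The SD would be 19√m, where m is the number of subjects in the MDMA source. The protocol does not give m. For an assumed m of 8 to 16 the SD is 53.7 to 76.0, and the paired requirement is 31 to 60 subjects.

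**Step 5. What 12 subjects can detect.** A paired test with n = 12 has 80% power at d = 0.889.
- If 19 is the SD of the difference: 0.889 × 19 = 16.9 points.
- If 19 is a per-condition SD with ρ = 0: 0.889 × 26.9 = 23.9 points.

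**The case against.** The best defence is that the paragraph is under-documented rather than miscalculated. It does not label ±19 and names no test. With 19 as a per-condition SD and no correlation the answer is 10, one subject from the stated figure. That stands as far as it goes, and it would be wrong to say that no plausible reading comes near 11. But it requires moving the ± from the change to each condition and assuming that two ratings from one person are unrelated. The protocol states neither, and even then 11 subjects have 87.5% power, not 80%.

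It is also fair that the consequence is small. With 19 as an SD the stated 80% is conservative, and no subject is exposed differently because of it.

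A reader might infer something stronger from section 4c, which in its opening paragraph enters dose as a between-subjects factor. Two separate groups with SD 19 would need 9 each (18 in all), and two groups of 6 would have only 63% power, so the trial might look underpowered. The documents do not support this. All 12 subjects take both conditions, and groups of 6 never exist. An analysis that ignored the pairing would still have 12 observations per condition and nominal power of about 93%. The 18 also treats 19 as a spread between people, whereas the paired 6 treats it as the spread of a difference.

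A reader might also object that insight is not among the measures named in hypothesis 2. That is not an error: the paragraph explains that self-report measures vary more than cardiovascular or hormonal ones, and that insight showed one of the smaller changes.

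**Conclusion.** The sample-size statement is wrong as written. At the stated alpha and power, 28±19 leads to 6 subjects if 19 is the SD of the within-subject difference, and to 10 if it is a per-condition SD with zero correlation. Neither is 11.

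The error lies in the stated basis, not in enrolment. On the two SD readings, 12 subjects have 99.6% and 90.7% power for 28 points. This conclusion assumes a normally distributed paired difference, no dropout, and that ±19 is an SD. Were it a standard error, 12 would fall well short, which is the main reason the label matters. Nothing in the text says that it is one.

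The assurance about other measures has no support beyond this figure. What can be said for those measures is that 12 subjects have 80% power for a paired difference of 0.89 of its own SD.

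**What to change.** Keep N = 12 and rewrite the Sample Size paragraph of section 4c:

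1. State what ±19 is: SD of the within-subject difference, per-condition SD, or standard error (then with the number of subjects in the MDMA source).
2. Name the within-subject test that the calculation assumes and, if 19 is a per-condition SD, the correlation.
3. Replace the statement that 11 subjects give 0.80 with the power 12 subjects have for 28 points: over 99% if 19 is the SD of the difference, about 91% if it is a per-condition SD with zero correlation.
4. Replace the closing assurance with the effect detectable at 80% power: 0.89 SD of the paired difference, which is about 17 points or about 24 points on those two readings.
5. Make the opening description of the ANOVA agree with the crossover, so that the test behind the power figure can be identified.

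The cost is one rewritten paragraph and a wording correction. Enrolment, procedures and data collection are unchanged. If the source shows that ±19 is a standard error, the adequacy of 12 would have to be reconsidered.

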Source and Storage of study drugs:  Under supervision of the Food and Drug Administration, we will synthesize MDA in our laboratory.  We will assess identity, stability, and purity to their satisfaction.  MDA will be stored and handled according to federal, state, and local regulations. MDA will be stored in our safe using procedures approved by the DEA.

Study Measures are similar or identical to those used in our past and ongoing studies to facilitate comparisons between MDA and related compounds.  Below we list timing of measures followed by measure descriptions.
Timing of Measures:
Plasma for MDA & Metabolites: Pre and 1, 2, 4, 6, 8, 12, 26, and 30 hrs after MDA or Placebo.
Urine for MDA & Metabolites: Urine samples at 0-8 and 24-48 hrs after MDA or Placebo dosing..
Plasma or serum (as appropriate) for oxytocin (which will be frozen and sent to [name]): Predose and 1, 2, 3, and 4 hours after dosing.  
Plasma or serum (as appropriate) for cortisol and prolactin: Predose, 2, and 3 hours after dosing.  

Heart rate, blood pressure, impedance cardiography, skin and core temperatures, visual analogue scales: Predose and 0.5, 1, 1.5, 2, 2.5, 3, 4, 6, 8, 24, and 30 hours after dosing 
BSI: Predose and 24 hours after MDA or Placebo (to measure possible residual drug effects).
Subjective drug effects questionnaire (SDEQ): At 7 hours after dosing and before discharge on Day 3. 
APZ-OAV and Hood M-Scale:  At 7.5 hours after dosing and before discharge on Day 3.
AVI and IAS-R: Predose, 2.5, 7.5 and 29 hrs after dosing and before discharge on Day 3.
Brief Fear of Negative Evaluation (BFNE) and State-Trait Anxiety Instrument – State (STAI):  Predose and once during peak drug effects (1 – 2.5 hours postdose).
Emotional Face Task and Famous Face task: During peak drug effects (1 – 2.5 hours postdose).
Dot Probe Task:  at 2hr. post dose.
Neurocognitive battery (Visual Functioning Battery):  3 hours after MDA or Placebo (to measure possible residual drug effects).
EEG:  3 hrs after MDA.
Written description of drug effects:  10 hours after dosing.

Descriptions of Measures
Pharmacokinetic and Hormonal Measures
Blood is sampled through an indwelling intravenous catheter placed by licensed medical personnel.  Each sample requires 7 ml or less, making the total required in each of the two experimental sessions 146 ml.
All urine is collected, with the pH determined before acidification and storage with timed samples reflecting predose and the 0-8 and 8-30 hrs after MDA.

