Limitations on Nicotine (Tobacco) and Caffeine Use: One important aspect of being in a hospital is that smoking is not allowed.  Smokers may feel irritable or anxious and it is likely that they will feel the desire to smoke.  We will ask that subjects use less than two cups of coffee (200 mg caffeine) on the day before and morning of the experimental session.  If subjects typically drink larger amounts of caffeinated drinks, he/she may feel irritable, tired, and may develop a headache. If they feel that it would be overly difficult for them to limit nicotine or caffeine intake, then they will be requested not to participate in this study.

Catheterization:  Study involves the insertion of a catheter into a forearm vein for blood sampling.  The longest the catheter is kept in place is 10 hours.  This has been well tolerated by subjects in previous studies.  Aseptic technique is always used in inserting the catheters and the risk of infection is small.  In order to reduce the discomfort of needle insertion, an ointment containing a local anesthetic (lidocaine) will be made available and applied to participants' arms if they choose.
  
Blood Loss: Total amount of blood withdrawal during the second screen visit and the post-study follow up will be approximately 51 ml. Blood withdrawal during the two challenge sessions will be approximately 146 ml per session. The total blood loss during this study period of about 4 weeks will be 343 ml. Slow removal of this amount of blood pose little risk to healthy subjects.

No subjects will be restricted from receiving standard therapies during the study.  We screen out subjects receiving therapies that do not fit our inclusion/exclusion criteria.  If therapies become medically necessary for a subject, that subject will be temporarily suspended or permanently discontinued from the study, as appropriate.

Risk of Loss of Confidentiality.  Confidentiality and Privacy.  There is a potential for loss of privacy for participants in this experiment.  The results of test scores, details of past drug history, past medical history, etc., will be kept confidential.  The investigators will do the best they can in keeping locked files and using code numbers wherever possible.  

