Nonetheless, it will be common knowledge that participants in this experiment are required to have past use of MDA or MDMA.  Therefore, in the consent form and in discussions, we caution potential participants that anyone having strong concerns about their past use of drug use being revealed should not participate in this research.  To minimize these risks, we are applying for a Certificate of Confidentiality.  

PROTECTION AGAINST RISK

Volunteer Discontinuation, Dropout or Dismissal.  A volunteer may drop out of the study at any time if he/she so chooses or if the investigator feels it is clinically appropriate.  A volunteer will be dismissed from the study due to a serious or unexpected adverse experience or a serious concurrent illness that warrants withdrawal of the subject from the study.  Subjects who use illicit drugs that could interact with study drugs or who otherwise fail to follow study procedures can be dismissed.  

Subject Safety Monitoring and Test Termination.  Using self-report questionnaires and a general medical exam with a physician, nurse, or nurse practitioner, subjects will be screened to eliminate those with significant medical or psychiatric problems.  Special attention is given to allergies and past adverse reactions to MDA, MDMA, and any other stimulants or hallucinogens. If adverse effects should occur, medical treatment will be immediately available. We have extensive experience in measurements in pharmacology/pharmacodynamic studies. A hospital maintained crash cart, oxygen and emergency ventilation equipment (Ambubags) are immediately available. Physiological monitoring of blood pressure, heart rate, body temperature, and subjective ratings will be carried out before dosing and until acute effects resolve (typically around 6 hrs) to ensure that there are no serious adverse physical or psychological effects of MDA.  Throughout the study, particular attention is paid to the rare MDMA-related acute hyperthermia that might also occur with MDA.  Methods of protecting against this risk are described below. 

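### The named repeated measures ANOVA, if run in its classical complete-case form, drops a volunteer from a measure for one missed reading, and 12 enrolled against a stated need of 11 leaves room to lose only one

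*Protocol*

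**What the plan says.** Section 4c (Methods of Data Analysis) describes the main analysis twice. Under Sample Size it says "Measures are analyzed using repeated measures ANOVA with condition and time as factors". Its opening paragraph says that the hypothesis measures are "analyzed by ANOVA with time as the repeated measure and dose as a between subject factor". Neither sentence says what happens to a volunteer with a gap.

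The sample size rests on a rating of insight after MDMA: "visual analog ratings for this item increased by 28±19 points compared to placebo". From this the protocol concludes that "a sample size of 11 is required, with a power of 0.80 and assuming a two-sided alpha of 0.05", and adds: "We will increase this N to 12 to allow balancing of dose order". Nothing is added for loss.

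The list of measurement times in 4b sets these for heart rate, blood pressure, impedance cardiography, skin and core temperature and the visual analogue scales: "Predose and 0.5, 1, 1.5, 2, 2.5, 3, 4, 6, 8, 24, and 30 hours after dosing". Other measures have fewer times, for example five for oxytocin and three for cortisol and prolactin.

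Section 5b foresees incomplete volunteers. If a therapy becomes medically necessary, "that subject will be temporarily suspended or permanently discontinued from the study, as appropriate". It also says "A volunteer may drop out of the study at any time if he/she so chooses".

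**The concern.** A classical repeated measures ANOVA with condition and time both within person works on a complete row per volunteer. One missed reading, or one missed session, removes that volunteer from that measure, however much else was collected. With 24 cells per row and 12 volunteers, a few scattered gaps can remove a sizeable share of the sample.

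Three things are at stake. The analysed number can fall below the 11 that the protocol itself says it needs. Different measures are then analysed in different subsets of volunteers. And each deletion can upset the order balance that is the only stated reason for the twelfth volunteer.

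**Working it through.** **Inputs.** From 4c: 28±19, power 0.80, two-sided alpha 0.05, 11 needed, 12 enrolled. From 4b: predose plus 11 times = 12 times, and 2 sessions, so 12 × 2 = 24 cells per volunteer and 12 × 24 = 288 cells in all. The missing rate m per reading is not in the protocol and is assumed to lie between 0.1% and 5%.

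**1. The protocol's own figure.** Paired t-test, exact noncentral-t power:
- 19 as the SD of the within-person difference: d = 28/19 = 1.474, and n = 6 gives power 0.820.
- 19 as the SD in each condition with zero correlation: d = 28/(19√2) = 1.042, and n = 10 gives 0.834. This comes close to 11.
- For n = 11 to give exactly 0.80, d must be 0.938, that is an SD of the difference of 28/0.938 ≈ 29.9, which the protocol does not state.

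The figure of 11 is therefore approached only under the conservative second reading. All three are carried forward.

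**2. The margin.** One incomplete volunteer leaves 11 and two leave 10. If two gaps fall at random among the 288 cells, the chance that they hit different volunteers is 1 − 12·C(24,2)/C(288,2) = 0.92.

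**3. Complete volunteers.** P(complete) = (1 − m)^24, expected N = 12 × P(complete), and the number complete is Binomial(12, P):

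| m (assumed) | P(complete) | Expected N | P(N < 11) |
|---|---|---|---|
| 0.1% | 0.976 | 11.7 | 0.03 |
| 0.5% | 0.887 | 10.6 | 0.40 |
| 1% | 0.786 | 9.4 | 0.76 |
| 2% | 0.616 | 7.4 | 0.97 |
| 5% | 0.292 | 3.5 | ~1.00 |

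The 24 h and 30 h readings of session 1 fall at the predose and 6 h times of session 2. Counting 22 distinct occasions instead of 24 gives P(N < 11) of about 0.36 at 0.5% and 0.72 at 1%, so little changes.

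**4. Average power over that binomial distribution (24 cells).**

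| m (assumed) | 19 = SD of difference | 19 = SD per condition, correlation 0 | 11 gives exactly 0.80 |
|---|---|---|---|
| 1% | 0.97 | 0.79 | 0.71 |
| 2% | 0.88 | 0.65 | 0.57 |
| 5% | 0.41 | 0.26 | 0.22 |

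At a fixed N = 10 the same three readings give 0.985, 0.834 and 0.752.

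**5. Measures with fewer times.** Six cells (cortisol, prolactin) at 2% missing: P(complete) = 0.98^6 = 0.886, expected N = 10.6, average power 0.986 or 0.855 under the first two readings. Ten cells (oxytocin) at 2%: 0.98^10 = 0.817, expected N = 9.8.

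**The case against.** The protocol never prescribes complete-case analysis. A reader might infer from the method's name that listwise deletion is planned, but the text does not say so. The same name is also used loosely for fits that keep partial data, and missing-data rules are commonly left to an analysis plan, which is not shown. This stands, so the point is conditional. What the protocol does fix is the method, and the usual meaning of that method is the fragile one.

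The missing rates are assumed. The stay is supervised and inpatient, with automated devices and a tympanic backup for core temperature. At 0.1% missing the expected complete number is 11.7. Gaps clustered within a volunteer also remove fewer people than independent gaps at the same rate. Both points stand.

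The 24-cell row is the worst case. Among the hypothesised measures only the cardiovascular ones have 12 times, and 4c expects those to show larger effects than self-report. This stands too, although the visual analogue scales on which the sample size was set are also taken at 12 times.

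Finally, the other ANOVA sentence in 4c makes dose a between-subject factor. Under it the row would be one person-session with 12 cells, and a volunteer with one session would be kept. But that model contradicts a design in which each volunteer receives both conditions, so it does not rescue the plan. It is a further reason to rewrite the paragraph.

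**Conclusion.** The point holds as a conditional weakness that is cheap to remove. If the ANOVA is run on complete cases, two volunteers with any gap in a 12-time measure leave 10, one below the stated need, and no allowance was made for this. The expected complete number ranges from 11.7 to 3.5 as the assumed missing rate goes from 0.1% to 5%.

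A reader might go further and infer that fewer than 11 means an underpowered trial. The documents do not support that. With 28±19 as stated, N = 10 still gives 0.985 or 0.834. Power at N = 10 falls below 0.80 (to 0.752) only if 11 is taken to give exactly 0.80, which needs an SD that the protocol does not report. At 1% missing, average power runs from 0.97 to 0.71 across the three readings, and the loss becomes large under every reading only towards 5%.

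These figures assume that gaps are independent across readings and that a paired t-test on the complete volunteers stands in for the ANOVA contrast.

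**What to change.** In 4c, replace both ANOVA sentences, including the one that makes dose a between-subject factor, with a linear mixed model fitted by REML to all available readings. Use condition, time and condition × time as fixed effects, a volunteer random effect, a within-session correlation structure named in advance, and small-sample degrees of freedom such as Kenward-Roger. Report the number of volunteers and readings used for each measure.

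This changes wording only and needs no new data. The cost is that a correlation structure must be chosen beforehand and that readings are assumed missing at random given those observed. The gain is mainly for scattered missed readings. A volunteer with only one session stays in the model but adds little to the within-person contrast, so the change does not make up for drop-out between sessions.
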